The safety and feasibility of the community-based exoskeleton gait training program assessed by recording adverse events and side effects, which will be split into two categories: (a) minor or anticipated side effects and (b) serious or unanticipated side effects. Feasibility will be assessed as a measure of compliance to study parameters, by determining whether the individual met the suggested dosage of device use while in the community.We will evaluate the primary endpoint (peak knee extension at midstance) as a function of dosage by comparing this parameter across multiple time points: Baseline to Initial Assessment (signals completion of in-lab accommodation/training block), Baseline to Intermediate Assessment (signals 50% completion of community use block), Baseline to Final Assessment (signals completion of community use block), and Baseline to Follow-up Assessment (signals 6-weeks post completion of community use block).We will evaluate changes in lower limb muscle spasticity after robotic exoskeleton gait training using the modified Ashworth scale and the Tardieu scale measured at two time points: the initial and final outcome assessment.

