**Fig 2 pone.0304087.g002:**
[figure not shown]
Schematic diagram of the randomized, cross-over protocol. Yellow indicates the 12-week block for exoskeleton set-up and in-lab accommodation. Pink indicates the 12-week block for community exoskeleton use, including a 6-week follow up period. Blue indicates the 12-week block for standard therapy in the community.

The design is structured as a randomized crossover study with two intervention arms: (i) exoskeleton intervention and (ii) standard therapy control (Fig 2). The crossover design was chosen to maximize participation by allowing all participants to receive the exoskeleton intervention. After enrollment, each participant will be randomized into one of two groups: Group A will receive the exoskeleton intervention first, followed by standard therapy control, while Group B will complete standard therapy control first before crossing over to receive the exoskeleton intervention. Continuation of the participant’s existing standard therapy was chosen as the control due to limited resources to administer a common program and because individuals in the target populations are often enrolled in a physical therapy regimen. All participants will complete an initial visit for exoskeleton fitting, setup, and calibration as well as multiple in-lab accommodation visits prior to starting the community-based exoskeleton intervention. An alternative option, if the participant is not able to complete the community use portion of the protocol for any reason, is to continue the intervention by completing a lab-based exoskeleton training consisting of 10 total visits, each with a target of 1-hour total of walking with the exoskeleton. The target intervention dosage in the community will be held constant across all subjects who participate at 1 hour/day, 5 days/week. Outcomes from individuals who complete the lab-based training will be analyzed separately from those who complete the community-based intervention. The maximum possible number of visits to NIH for completion of this study is 19. All visits will take no more than 4 hours to complete. There will be up to six outcome assessments to evaluate our primary, secondary and exploratory objectives.

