
### Study assessments and outcomes

All participants will complete the same study procedures and assessments (S1 Table), only varying in order of completion by Group (Fig 2). Each assessment visit will include collection of all outcome measures as indicated in Table 1. For Group A, assessments will be performed in the following order: at baseline (upon enrollment), initial outcome assessment (after in lab accommodation), intermediate outcome assessment (6 weeks after start of community exoskeleton intervention), final outcome assessment (12 weeks after start of community exoskeleton intervention), follow up outcome assessment (6 weeks after completing community exoskeleton intervention), and standard outcome assessment (12 weeks after starting standard therapy control). For Group B, assessments will be performed as follows: baseline assessment, standard outcome assessment, initial outcome assessment, intermediate outcome assessment, final outcome assessment, and follow up outcome assessment.

**Table 1 pone.0304087.t001:** Outcome measures by ICF domain and data collection timepoints.

Outcome Measure	ICF Domain^1^	Baseline Assessment	Exoskeleton Intervention Assessments				Standard Outcome Assessment
			Initial	Intermediate	Final	Follow-Up	
Peak knee extension (deg)	Body structure	X	X	X	X	X	X
Knee extension at initial contact (deg)	Body structure	X	X	X	X	X	X
Step length (m)	Function	X	X	X	X	X	X
Gait speed (m/s)	Function	X	X	X	X	X	X
Knee moment in stance phase (Nm)	Function	X	X	X	X	X	X
Peak activation of knee extensor (mV/mV)	Function	X	X	X	X	X	X
Mean knee extensor muscle activation (mV/mV)	Function	X	X	X	X	X	X
Gross motor function classification system (GMFCS, I-V)	Function	X	X	(X)^2^	X	X	X
Pediatric evaluation of disability inventory–computer adaptive test (PEDI-CAT, scaled 20–80)	Activity	X	X	(X)	X	X	X
Gross motor function measure (GMFM-66, scored 0–198)	Activity	X	X	(X)	X	X	X
6-minute walk test (6MWT, m)	Function	X	X	(X)	X	X	X
Timed up and go (s)	Function	X	X	(X)	X	X	X
Knee extensor spasticity (Modified Ashworth scale, 0–4)	Body structure	X	X	(X)	X	X	X
Knee extensor spasticity (Tardieu scale, deg)	Body structure	X	X	(X)	X	X	X
Knee extensor isometric strength (Nm)	Function	X	X	(X)	X	X	X
Knee flexor isometric strength (Nm)	Function	X	X	(X)	X	X	X
Quebec User Evaluation of Satisfaction with Assistive Technology 2.0 (QUEST 2.0)	Activity				X		

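### All four exploratory dosage contrasts start at Baseline, so in Group B each one includes the 12-week standard-therapy block that precedes any exoskeleton use

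*Protocol article*

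**What the plan says.** In the protocol article, Objectives and endpoints, one exploratory objective is to study the primary measure "as a function of dosage by comparing this parameter across multiple time points". Four contrasts are listed, all from the same starting visit and each tied to a stage of exoskeleton use:

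- The first is given as "Baseline to Initial Assessment (signals completion of in-lab accommodation/training block".
- The second ends at the Intermediate visit and is said to mark the halfway point of community use.
- The third ends at the Final visit, when community use is over.
- The fourth is given as "Baseline to Follow-up Assessment (signals 6-weeks post completion of community use block".

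No distinction is made between the randomised groups.

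The treatment order is given under Study design, in the text after the Fig 2 caption: "Group B will complete standard therapy control first before crossing over to receive the exoskeleton intervention". The caption gives the length of the control block: "Blue indicates the 12-week block for standard therapy in the community". It gives 12 weeks for set-up and in-lab accommodation as well.

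Study assessments and outcomes places Baseline at enrolment and sets out the visit order: "For Group B, assessments will be performed as follows: baseline assessment, standard outcome assessment, initial outcome assessment", then Intermediate, Final and Follow-up. In Group A the Standard Outcome Assessment comes last.

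Statistical considerations assigns a repeated measures ANOVA to the dosage analysis and mentions neither a sequence term nor a group-specific reference visit.

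**The concern.** The same label describes two different quantities. In Group A, Baseline to Initial covers set-up and accommodation. In Group B it covers those plus a complete standard-therapy block with no exoskeleton exposure, and the extra block carries forward into the other three contrasts.

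The article itself gives reasons to expect change over those 12 weeks. The Discussion points to growth, development and ongoing physical therapy, and says the standard-therapy period is there to control for growth. Study population describes the gait pathology as progressive.

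Two readings are at stake. One is the accommodation step, for which Baseline to Initial is the only listed contrast. The other is the cumulative change up to Follow-up. In a combined mean, both would mix exoskeleton exposure with standard-therapy time from one group and average over two different elapsed times.

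**Working it through.** The plan gives no figure of its own on this point, so there is none to reproduce. The check uses the stated visit order and block lengths.

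**Inputs**
- Set-up and accommodation block: 12 weeks (Fig 2 caption).
- Standard-therapy block: 12 weeks (Fig 2 caption; Study assessments and outcomes).
- Intermediate and Final: 6 and 12 weeks after community use starts. Follow-up: 6 weeks after it ends (Study assessments and outcomes).
- Group B share p: not stated. Assumed 0.5, range 0.4 to 0.6.
- Change g in peak knee extension over the standard-therapy block: not stated. Assumed 1 to 3 degrees, either sign.

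**Step 1: nominal weeks from Baseline.** Group A: 12; 12 + 6 = 18; 12 + 12 = 24; 24 + 6 = 30. Group B: add 12 to each.

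| Contrast from Baseline to | Group A | Group B | Ratio B/A | Standard therapy as share of Group B interval |
|---|---|---|---|---|
| Initial | 12 | 24 | 2.0 | 12/24 = 50% |
| Intermediate | 18 | 30 | 1.67 | 12/30 = 40% |
| Final | 24 | 36 | 1.5 | 12/36 = 33% |
| Follow-up | 30 | 42 | 1.4 | 12/42 = 29% |

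The share in Group A is 0% throughout.

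**Step 2: effect on a pooled contrast.** For visit k, let a(k) and b(k) be the mean changes in Groups A and B since the last assessment before the exoskeleton phase. The contrast from Baseline has mean a(k) in Group A and b(k) + g in Group B. The pooled mean is

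(1 − p) × a(k) + p × (b(k) + g) = [(1 − p) × a(k) + p × b(k)] + p × g.

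The unwanted term is p × g, the same for all four visits.

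**Step 3: size.**
- p = 0.5: 0.5 × 1 = 0.5 to 0.5 × 3 = 1.5 degrees, either sign.
- p from 0.4 to 0.6: 0.4 × 1 = 0.4 to 0.6 × 3 = 1.8 degrees, either sign.

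With the planned 13 evaluable children per diagnostic pool, an even split is 6 and 7, so p is 6/13 = 0.46 or 7/13 = 0.54 at best.

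**Step 4: after re-referencing.** Counting Group B from its Standard Outcome Assessment subtracts 12 weeks from each interval. Both groups then have 12, 18, 24 and 30 nominal weeks, and the p × g term disappears.

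**The case against.** The case for treating this as minor has several parts.

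- **Constant shift.** The term p × g is the same in all four contrasts, so it cancels when Intermediate, Final and Follow-up are compared with Initial or with each other. This stands. The damage is confined to the accommodation step and the cumulative levels from Baseline.
- **The ANOVA may not use Baseline.** Statistical considerations refers to four outcome assessments, and Table 1 groups exactly four under the exoskeleton intervention, without Baseline. On that reading the ANOVA escapes. The contrasts written into the objective still start from Baseline.
- **Labels mark visits, and pooling is inferred.** The labels say which stage a visit completes and make no causal claim. Nor does the article say outright that the groups are averaged regardless of sequence. Both are fair, but the objective is about dosage, and following its text folds undosed time into one group only. The reference visit is stated rather than left open, so this is not detail deferred to a fuller document.
- **Exploratory and small.** No primary or secondary conclusion depends on these contrasts. At the assumed extreme, 1.5 degrees compares with a 10-degree clinical threshold. With a planning SD of 3 × 4 = 12 degrees and n = 13, the standard error is 12/√13 ≈ 3.3 degrees, so the shift is about 1.5/3.3 = 0.45 of a standard error. This limits the priority. Unlike sampling error, though, the shift does not shrink with more children.
- **Nominal weeks.** The Group B figures assume that set-up starts after standard therapy ends. Fabrication typically takes 4 to 6 weeks (Intervention and dosage). If it ran during standard therapy, Group B would reach Initial at 24 − 6 = 18 to 24 − 4 = 20 weeks. The standard-therapy block would still lie inside every Group B contrast.
- **Existing safeguards.** The first-period restriction covers only the comparison of exoskeleton with standard therapy. The growth covariate in the Discussion is conditional and does not change the reference visit. Neither repairs the contrasts.

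**Conclusion.** The concern holds. The Baseline reference fits Group A and is wrong for Group B, where it places a 12-week standard-therapy block inside all four contrasts. That block is 50% of the nominal Baseline-to-Initial interval and 29% of the interval to Follow-up.

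The shift in a pooled contrast is p × g: 0.5 to 1.5 degrees in either direction at 1:1 allocation, or 0.4 to 1.8 degrees if 40% to 60% of children are in Group B. The allocation share and the 1-to-3-degree change are assumptions, because the article gives neither. The order of visits is explicit; the exact weeks are nominal.

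The consequence is limited to an exploratory objective. The primary endpoint uses Initial to Final and is not touched. The change should still be made, because dosing is part of the study's stated purpose and Baseline to Initial is the only planned reading of the accommodation step.

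**What to change.** In Objectives and endpoints, replace Baseline in the four dosage contrasts with the last assessment before the exoskeleton phase: Baseline for Group A and the Standard Outcome Assessment for Group B. Keep Group B's change from Baseline to Standard Outcome Assessment solely as a standard-therapy change.

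In Statistical considerations, say whether the repeated measures ANOVA includes a pre-exoskeleton visit, since the objective names five time points and the analysis text four assessments. If it does, use the same group-specific reference.

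The cost is about one sentence in each place. Table 1 already schedules peak knee extension and the other gait measures at the Standard Outcome Assessment, so no visit or measurement is added. The change puts both groups on the same footing. It does not remove growth during the exoskeleton phase itself, so these remain within-child changes without a concurrent control.

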### Study design

This study has been approved by the Institutional Review Board of the National Institutes of Health and is registered on clinicaltrials.gov (NCT05726591). It is a single site outpatient study with all data collection to occur at the National Institutes of Health Clinical Center, Rehabilitation Medicine Department, Neurorehabilitation and Biomechanics Section and is analogous to a phase I/II clinical trial. Interventions and up to six outcome assessments will be conducted according to the schedule outlined in Figs 1 and 2.

**Fig 1 pone.0304087.g001:**
[figure not shown]
Enrollment, interventions and assessment chart for Group A and Group B.

**Fig 2 pone.0304087.g002:**
[figure not shown]
Schematic diagram of the randomized, cross-over protocol. Yellow indicates the 12-week block for exoskeleton set-up and in-lab accommodation. Pink indicates the 12-week block for community exoskeleton use, including a 6-week follow up period. Blue indicates the 12-week block for standard therapy in the community.

The design is structured as a randomized crossover study with two intervention arms: (i) exoskeleton intervention and (ii) standard therapy control (Fig 2). The crossover design was chosen to maximize participation by allowing all participants to receive the exoskeleton intervention. After enrollment, each participant will be randomized into one of two groups: Group A will receive the exoskeleton intervention first, followed by standard therapy control, while Group B will complete standard therapy control first before crossing over to receive the exoskeleton intervention. Continuation of the participant’s existing standard therapy was chosen as the control due to limited resources to administer a common program and because individuals in the target populations are often enrolled in a physical therapy regimen. All participants will complete an initial visit for exoskeleton fitting, setup, and calibration as well as multiple in-lab accommodation visits prior to starting the community-based exoskeleton intervention. An alternative option, if the participant is not able to complete the community use portion of the protocol for any reason, is to continue the intervention by completing a lab-based exoskeleton training consisting of 10 total visits, each with a target of 1-hour total of walking with the exoskeleton. The target intervention dosage in the community will be held constant across all subjects who participate at 1 hour/day, 5 days/week. Outcomes from individuals who complete the lab-based training will be analyzed separately from those who complete the community-based intervention. The maximum possible number of visits to NIH for completion of this study is 19. All visits will take no more than 4 hours to complete. There will be up to six outcome assessments to evaluate our primary, secondary and exploratory objectives.

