A baseline gait analysis walking with their usual assistive devices (i.e. AFO, walker, crutches) using motion capture and EMG, will be used to set the initial parameters of the device after fabrication, which typically takes 4–6 weeks. After this time, the participant will return to the lab for fit-testing, calibration and tuning of the exoskeleton control parameters. As part of this process, the primary exoskeleton mode will initially be set to the Resist Mode, which applies resistance to knee extension during stance and swing phase. In this tuning phase, the torque profile is customized to each participant by specifying the magnitude and ramp rate of the torque provided during each of the five gait phases (Fig 3B). If the participant is unable to ambulate in this mode, the primary mode will revert to the Interleaved Mode, which assists extension during stance and resists it during swing. Additionally, a secondary Assist Mode of operation will be set for each participant. Prior to taking the device home for the community intervention training, each participant and their caregiver must complete an up to 10 visit accommodation period for walking in the primary and secondary modes. These sessions will consist of walking overground across various surfaces and environments at the hospital, including tile, laminate and carpet indoors, as well as outdoor pathways with inclines and declines and concrete sidewalks. Clinical observation by study physical therapists, as well as analysis of exoskeleton sensor data during each type of walking, will be completed to ensure safe operation and optimal exoskeleton controller performance across the conditions and modes. The accommodation period also includes education of the participant and parent/caretaker on how to don/doff the exoskeleton, how to operate its software to turn it on/off, and how to charge the battery. The participant will be allowed to take the device into the community for 12 weeks of intervention if the user, their caregiver and the study team members are comfortable with their competency using the device. All control parameters will be set before the user takes the device home, so they will not be required to tune the device outside of the clinical setting. The participant will receive a laptop computer with software that enables the user to switch between operational modes as well as complete virtual telehealth visits with the study team. The custom software also enables the user or study team to collect sensor data from the exoskeleton during the weekly virtual visits, which will be used to verify the exoskeleton operation each week and make any changes to the controller parameters, if necessary. The participant will be instructed to utilize their primary mode for exoskeleton training, with a target of 1 hour/day for 5 days/week. They will be permitted to use the secondary Assistive Mode, if desired, after completing the primary mode training for the day, or on days when training is not prescribed. Participants are asked to complete a log of their exoskeleton use during the intervention period, including the number of minutes and mode of operation for each day. During the community intervention period the study team will set up weekly check-ins with the participant. These sessions are utilized to confirm there are not fit or operational issues with the exoskeleton and to review participant compliance with training procedures and provide encouragement to continue or enhance compliance if necessary. If any technical issues with the device were to arise, the user will be instructed to contact the study team immediately rather than wait for the weekly check-in appointment. If repairs or maintenance to the exoskeleton are necessary, the study team will travel to the participant to complete them as soon as possible.

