Our continuous data outcomes will be summarized using descriptive statistics and presented as means with standard deviation. We will summarize our categorical data as a range with percentages. The primary endpoint, peak knee angle at midstance, will be analyzed using a per-protocol analysis to include all participants who completed at least 80% (9 weeks) of the study intervention in the community using a paired t-test between the initial and final outcome assessments. Similarly, a paired t-test will be utilized to compare change in the primary endpoint of peak knee extension with the change observed over the 12-week standard therapy block. Given the potential for carryover effects, this secondary outcome will only be assessed using data from the first intervention period from each group. We will test for normality and if not found, we will use the signed rank test instead of the paired t-test. Given the potential heterogeneity within each participant pool, we anticipate the possibility for a wide range of responses in the endpoints following the intervention. To address this potential variability, we will also perform a post-hoc linear regression analysis to assess potential effects of age, weight/height, and mobility (characterized by functional scale GMFCS I-IV) on each endpoint. We will perform an interim analysis of the primary endpoint when we have reached 50% of the estimated recruitment number to evaluate the effect and the power and revise the total enrollment number if indicated.

The same statistical procedures will be used for the secondary outcome measures and exploratory outcome measures that evaluate continuous data between multiple time points. We will report the 95% confidence intervals, in addition to the mean difference and statistical significance of that difference, for each endpoint. For the exploratory analysis of dosage effect across all four outcome assessments, we will use a repeated measures ANOVA.

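### Children who move to lab training: the two set rules overlap for late switchers, and analysing lab completers separately thins only Group A in the first-period comparison

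*Protocol article*

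**What the plan says.** The Study design section (text below Figure 2) opens an alternative route "if the participant is not able to complete the community use portion of the protocol for any reason". The route is "lab-based exoskeleton training consisting of 10 total visits, each with a target of 1-hour total of walking with the exoskeleton". No time limit is given, so the wording covers children who never take the device home and children who stop part-way. The rule for their data follows: "Outcomes from individuals who complete the lab-based training will be analyzed separately from those who complete the community-based intervention."

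Statistical considerations defines the primary analysis as per-protocol, to "include all participants who completed at least 80% (9 weeks) of the study intervention in the community". It makes no exception for a child who later has lab sessions.

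The same section limits the comparison of exoskeleton with standard therapy to each group's first period because of possible carryover, and the Discussion repeats this. Group A has the exoskeleton first and Group B has standard therapy first.

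On dose, the plan says: "The target intervention dosage in the community will be held constant across all subjects who participate at 1 hour/day, 5 days/week." A child judged competent is "allowed to take the device into the community for 12 weeks of intervention".

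The sample-size paragraph expects 80% of enrolled children to reach the final assessment and 25% to complete the protocol without the community part. It recruits 22 per pool to retain 13.

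**The concern.** There are two problems of unequal weight.

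The first is an assignment gap. The two rules are not mutually exclusive, and the article does not say which one governs when a child satisfies both. In a pool with 13 planned evaluable children, placing even one child after the results are known is a choice better made beforehand.

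The second is more important. The first-period comparison is the only one between treatments, and randomisation is what makes it credible. The separate-analysis rule takes children out of Group A because of something that happens after randomisation, during the very period being compared, and that may depend on tolerance or response. Group B's first period offers no such exit. The comparison then sets Group A children who managed home use against Group B children who faced no such test. If children who leave home use would have changed differently on any regimen, the contrast carries that difference along with the treatment effect.

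**Working it through.** **Inputs.** From Statistical considerations: 13 evaluable and 22 recruited per pool, 80% completion, 25% electing out, 9-week threshold. From Study design and Intervention and dosage: 1 hour a day, 5 days a week, 12 weeks; lab option 10 visits of 1 hour.

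**1. The plan's own figure.** 13 / (0.80 × 0.75) = 21.67, rounded up to 22, as stated. Subtracting both losses would give 13 / 0.55 = 23.6, that is 24, which does not match. The 25% therefore acts on completers:
- completers per pool: 22 × 0.80 = 17.6
- community: 17.6 × 0.75 = 13.2
- lab: 17.6 × 0.25 = 4.4

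**2. Where the rules overlap.** Target hours are 12 × 5 × 1 = 60 for the full community block, 10 × 1 = 10 for the lab option, and 9 × 5 = 45 at the threshold. A child who stops after w full weeks and then completes the lab visits has 5w + 10.

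| Community weeks before lab | Target hours | 9-week rule | Lab rule | Result |
|---|---|---|---|---|
| 0 | 10 | out | separate | agree |
| 4 | 30 | out | separate | agree |
| 8 | 50 | out | separate | agree |
| 9 | 55 | in | separate | conflict |
| 11 | 65 | in | separate | conflict |

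The conflict is confined to stops from 9 to under 12 weeks. The plan gives the threshold both as 80% and as 9 weeks. Since 0.80 × 12 = 9.6 and 9 / 12 = 75%, these differ slightly; I use the 9 weeks.

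**3. The first-period comparison.** The article gives no allocation ratio, so I assume equal allocation, 11 per group per pool. I also assume that those who elect out complete the lab route, the only alternative offered.
- Completers in each group: 11 × 0.80 = 8.8
- Group A moved to the lab: 8.8 × 0.25 = 2.2
- Group A left in the comparison: 8.8 − 2.2 = 6.6
- Group B moved to the lab in its first period: 0, leaving 8.8 (possibly more, as the 80% refers to the later final assessment)

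**4. How far the Group A mean could move.** Let H be the mean change among Group A children who stay in community use and L the mean among those who move to the lab. All Group A completers average 0.75H + 0.25L; the filtered group averages H. The shift is 0.25 × (H − L). The documents give no value for H − L. If it lay between 0° and the 10° target improvement, the shift would be 0° to 2.5°. Part of it would reflect fewer training hours and part selection, and the documents cannot separate the two.

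**The case against.** **A late switch hardly fits the visit cap.** The plan allows 19 visits in all. Ten accommodation visits plus ten lab visits make 20 before any assessment. One fitting visit, six assessments and ten lab visits make 17, leaving two for screening and accommodation. The ten lab visits may therefore include accommodation, or the option may be meant mainly for children who never start home use, as the 25% electing out suggests. This largely stands: late switchers should be rare, and 65 hours is an upper bound on one reading. It does not close the gap, because accommodation is only capped at ten: 3 + 10 + 6 = 19 fits if fitting and screening share those visits. Nor does it touch the first-period problem, which arises equally if every lab child is a never-starter.

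**This is a complaint about per-protocol analysis.** In part, yes. For the within-child primary endpoint, a per-protocol set is a declared choice in an early-phase trial, and keeping a 10-hour regimen apart from a 60-hour one is reasonable. The between-treatment comparison is different, because the exclusion can arise within the compared period in one group only.

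**The rule might cover the whole record of a lab completer.** A Group B child who moves to the lab in the second period might then also lose first-period data. The filter would no longer be one-sided in numbers, but control data would be dropped because of an event after they were collected. The text does not ask for this clearly, and I have not assumed it.

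**An article leaves detail to the full protocol.** That disposes of some points. The final visit is dated as "final outcome assessment (12 weeks after start of community exoskeleton intervention", which gives no date for a child who never starts home use; that, and the layout of the lab summary, may be settled elsewhere. The two assignment rules are stated in the article itself.

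**Conclusion.** The point holds in two parts. The set rules overlap for a child with 9 to under 12 community weeks who then completes lab training; this is real but narrow. Of more consequence, the separate-analysis rule thins the first-period comparison after randomisation in Group A alone, by about a quarter of its completers on the plan's own rates (2.2 of 8.8 per pool with equal allocation). The direction and size of any resulting bias cannot be derived from the documents. The 0° to 2.5° shift is an illustration under an assumed range.

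A reader might infer that neither analysis set can be interpreted. The documents do not support that. The primary set holds no child below 45 target hours, and the 10-to-65-hour spread is confined to a lab set of about 4 per pool on which nothing is powered. Children who stop at week 4 or week 8 create no conflict, since the 9-week rule already keeps them out of the primary set.

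A reader might also conclude that every child who starts home use belongs in the main community set. That would contradict the 9-week rule, admit a child with one home week plus the lab visits (5 + 10 = 15 target hours), and change the target population from completers to starters. The text gives no ground for it.

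**What to change.** 1. State that the 9-week rule takes precedence: a child with at least 9 community weeks stays in the primary set whether or not lab sessions followed. The lab summary then holds only children below that threshold, is descriptive, and reports home and lab hours for each child.
2. Add a stated supporting analysis of the first-period comparison that keeps every child with an outcome assessment, including those who moved to lab training, in the randomised group. Name the assessment used for those children.

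Both changes are wording. They use assessments already planned, add no visits and leave recruitment at 22 per pool. The downside is that the exoskeleton effect in the supporting analysis may be somewhat diluted, since some Group A children will have had far fewer training hours. Shown beside the planned analysis, it tells the reader how much the result depends on who stayed with home use.
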